### Adjunct project I: Identifying key therapeutic components and competence as predictors of outcome in DBT-PTSD and CPT

#### Background

Treatment integrity, defined as the extent to which treatment is implemented as intended, is not only required in order to draw valid conclusions from clinical trials, but is also implicated as a key ingredient of treatment success [94, 95]. Treatment integrity includes 3 components: 1) treatment adherence, which refers to the degree of utilization of techniques as specified in a manual, 2) treatment differentiation, which implies that treatments in a study differ on relevant dimensions; and 3) therapeutic competence, which is defined as how well these techniques are delivered and adapted to the specific therapeutic context [96].

In controlled clinical trials, it is currently standard practice to control for treatment integrity by using adherence ratings, but there are considerably fewer studies assessing therapeutic competence and its relationship to outcome [95, 97, 98]. With respect to established treatments of PTSD, there are no published studies investigating adherence and competence as predictors of outcomes. One study investigated these variables in gestalt-derived treatment for survivors of CA, but only 54% of the sample met PTSD DSM-IV criteria [99]. Competence here was not significantly related to changes in interpersonal stress and emotional resolution; it should be noted, however, that ratings were delivered by non-expert raters. In contrast, previous trials with other disorders [100, 101] indicate that competence is a significant predictor of outcome and a better predictor than adherence. In both studies, improved methods to assess competence were used, which also covered specific treatment components.

Based on the finding that therapeutic alliance has been more consistently found to correlate with treatment outcome than competence correlates with treatment outcome [102, 103], it has often been argued that common factors may be more important than competences related to the specific treatment. However, findings from a meta-analysis [98] suggest that therapeutic alliance may be considered as a moderator of the relationship between competence and outcome, as indicated by larger effect sizes in studies that did not control for the influence of therapeutic alliance.

The present study aims at identifying therapeutic competencies that are predictive for effective treatment of PTSD, as well as its associations with adherence and alliance. In addition, the present study provides the possibility to compare two treatments, DBT-PTSD and CPT, with respect to general aspects of competence common to cognitive-behavioural treatments. Finally, the contribution of particular components of general and specific therapeutic competence to treatment response in both treatments, will be subject to secondary, exploratory analyses.

#### Hypotheses

Therapists’ general therapeutic competencies will significantly predict treatment response (pre-post-changes of CAPS) in both treatments.Therapists’ DBT-PTSD–specific competencies will significantly predict treatment response at post-treatment in DBT-PTSD.Therapists’ CPT–specific competencies will significantly predict treatment response at post-treatment in CPT.

We expect that both general (hypothesis 1) and specific competencies (hypotheses 2a and 2b) will contribute significantly to the prediction of treatment response at post-treatment when controlling for pre-treatment severity of PTSD (pre-treatment scores of the CAPS) and BPD (pre-treatment scores of the BSL) as well as adherence and therapeutic alliance. To test hypotheses 2a and 2b, general competencies will also be controlled for.

#### Method

Assessments: Primary outcome measure will be the CAPS-5 [83]. Therapeutic competence will be assessed by two independent and extensively trained clinician raters who are blind to treatment outcome, using rating scales that have been specifically developed on the basis of the manuals applied in this trial (i.e. [104]).

Observer ratings of competence and adherence will be obtained from two randomly selected videotaped sessions per patient, covering two different treatment phases. The level of ratings averaged over the two phases will enter the path analyses. To assess general competencies, the Cognitive Therapy Scale [105] will be applied. This scale comprises 15 items (e.g., homework, guided discovery, efficient use of time, etc.). Items are rated on a scale ranging from 0 to 6, referring to the quality of implementation of interventions. The DBT-PTSD Competence Rating Scale [106] comprises 6 items referring to components specific for DBT-PTSD, such as appropriate implementation of skills. The CPT Competence Rating Scale [104] comprises 4 items reflecting competencies specific for CPT, such as identification of stuck points and optimal application of worksheets. For both treatment specific competence scales, items are rated on a scale from 0 to 6, and according to a detailed raters’ manual referring to the quality of implementation of interventions.

Adherence ratings will be assessed using the DBT-PTSD Adherence Rating Scale and the CPT Adherence Rating Scale, respectively, which both have been developed by our workgroup (i.e. [76]). To rate competence and adherence for one treatment session, on average 2 h are required.

All rating scales which have been developed to assess treatment integrity of DBT-PTSD and CPT as used in the present RCT have been evaluated for their psychometric properties e.g., with respect to inter-rater reliability (i.e., [76, 104]).

Therapeutic alliance will be assessed using the Helping Alliance Questionnaire [107]. This rating scale is an 11-item questionnaire that assess therapeutic alliance from both the patient’s and the therapist’s perspective. For example the patients’ version consists of 11 subtypes of patients’ helping alliances (e.g., the patient feels optimism and confidence that the therapist can help; the patient shares with the therapist similar conceptions of the aetiology of the problems). These components are rated on a 6-point Likert scale.

Data analyses: Path analyses will be carried out to determine the effects of the predictor variables listed above. For all hypotheses, differences in CAPS-5-scores at pre- vs. post (T6) will be specified as the criterion variable. For hypothesis 1, path analyses models with general competencies as predictor variables will be specified. For hypotheses 2a and 2b, path analyses models with the specific therapeutic competencies as predictor variables will be specified. For all hypotheses, path analyses models with pre-treatment severity of PTSD and BPD (pre-treatment scores in the CAPS-5, pre-treatment scores in the BSL) as well as therapeutic adherence and therapeutic alliance as additional predictor variables will be carried out. For hypotheses 2a and 2b, general competence will also be included into the path analysis. For hypothesis 1, a multi-sample path analysis with the grouping variable treatment condition (DBT-PTSD vs. CPT) will be performed. Path analyses allow us to specify correlations between predictor variables, and will be carried out using Mplus version 7 [108]. Mplus offers several advantages for data analysis, such as effective ways of missing value imputation (FIML) and dealing with multi-level (nested) data.

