#### Power analyses

The sample size was determined from a formal power analysis. The study was designed to have sufficient statistical power (1-β ≥ 0.80) to detect a supposed medium-size superiority of DBT-PTSD over CPT for the time*treatment interaction. A no more than medium between-group effect-size (d = 0.5, which corresponds to an effect-size f(V) of 0.354 for the time*treatment contrast for DBT-PTSD vs. CPT within a repeated measures design) was assumed since CPT was supposed to be substantially more efficacious than the TAU-WL condition to which DBT-PTSD has been previously compared. Under these assumptions, data from 70 participants per group are required to achieve sufficient statistical power (1-β ≥ 0.80) for Hypothesis 1. For Hypothesis 2 (“the superiority of DBT-PTSD is related to the severity of BPD-symptoms at baseline”) the power analysis indicated that a sample-size of at least 90 per group is needed to achieve sufficient statistical power to detect a clinically meaningful incremental R^2^ of at least 0.1 within a regression model. Accordingly, the recruitment target was set at a minimum of 180 participants (90 per group) to be randomised. In order to recruit and treat a minimum of 180 patients within 2 years, the study is conducted at three large German centres: the Central Institute of Mental Health in Mannheim, the Institute of Psychology, Goethe University in Frankfurt, and the Institute of Psychology, Humboldt University in Berlin.

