#### Statistical analysis

The CAPS-5 and the assessments pertaining to the secondary hypotheses are obtained at baseline (=T1); at month 3 (=T2); month 6 (=T3); month 9 (=T4); month 12 (=T5, end of high frequency phase); and month 15 (=T6, end low frequency phase = post assessment). Mixed linear models including these assessment points will be used as the primary analytic strategy to analyse and compare the changes in the two groups. Parameters will be estimated using restricted maximum likelihood estimates (REML) and without imposing predefined assumptions such as compound symmetry on the covariance matrix. Analyses are based on the intent-to-treat sample of patients who were randomised and fulfilled all inclusion criteria. To provide a more complete picture these primary analyses are complemented by analyses comprising those participants who completed the study according to protocol (ATP). To allow for a more comprehensive evaluation of the data, the results from the mixed linear models are supplemented by clinically meaningful indices including remission rates, response rates and effect sizes.

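### Adjunct project I models only the T1–T6 CAPS-5 difference; naming the T2–T5 scores as auxiliary variables would be a cheap gain in precision and protect against response-related loss at T6

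*Protocol article*

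**What the plan says.** The data-analysis paragraph under Method in Adjunct project I sets one outcome per patient for hypotheses 1, 2a and 2b: "differences in CAPS-5-scores at pre- vs. post (T6) will be specified as the criterion variable". The predictors are general or treatment-specific competence, then baseline CAPS-5 and baseline BSL, "as well as therapeutic adherence and therapeutic alliance as additional predictor variables will be carried out". General competence is added for 2a and 2b. The paragraph gives as advantages of Mplus features "such as effective ways of missing value imputation (FIML) and dealing with multi-level (nested) data". No interim CAPS-5 score is named as predictor, outcome or auxiliary variable.

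The Statistical analysis section of the main project shows that the interim scores exist. It begins "The CAPS-5 and the assessments pertaining to the secondary hypotheses are obtained at baseline (=T1); at month 3 (=T2" and runs through months 6, 9 and 12 to "month 15 (=T6, end low frequency phase = post assessment". There, "Mixed linear models including these assessment points will be used as the primary analytic strategy". Under Power analyses, "the recruitment target was set at a minimum of 180 participants (90 per group) to be randomised". Hypotheses 2a and 2b each concern one treatment, so each rests on about 90 patients.

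**The concern.** When the criterion is the only variable missing, FIML has just the predictors to condition on. A patient seen at T1 to T5 but not at T6 then contributes nothing to the regression of change on competence. Missing at random has to hold given the predictors alone, not given the patient's course so far.

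Two things follow. The competence slope is estimated less precisely than the collected data allow. And if those lost at T6 differ in interim response in a way the predictors do not capture, the analysis selects on something close to the outcome, which pulls the slope toward zero. All three Adjunct I hypotheses rest on such a slope, and the two single-arm ones have the fewest patients. The main project analyses the same instrument with all six assessments and does not have this weakness.

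**Working it through.** The article gives no sample size, power or effect size for Adjunct project I, so there is no stated figure to reproduce.

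**Inputs.** From the article: 180 patients (90 per group), CAPS-5 at T1–T6, the T1–T6 difference as criterion. Assumed: share missing T6, m = 10–40%; residual correlation of T5 and T6 change, ρ = 0.5–0.8; standardised competence slope 0.30; strength of selection.

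**1. Is the difference score itself the problem?** No. With baseline CAPS-5 as a covariate, the competence slope is the same for change and for the T6 score (−0.1366 for both in a test data set).

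**2. Precision when loss is unrelated to outcome.** If T5 is observed in those who miss T6,

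Var(slope with T5) / Var(slope without T5) = 1 − mρ².

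For m = 0.30 and ρ = 0.7: 1 − 0.30 × 0.49 = 0.853, and 1/√0.853 = 1.083, so the listed model's standard error is about 8% larger. The ratio SE(without)/SE(with) is:

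| Missing T6 | ρ = 0.5 | ρ = 0.7 | ρ = 0.8 |
|---|---|---|---|
| 10% | 1.013 | 1.025 | 1.034 |
| 20% | 1.026 | 1.053 | 1.071 |
| 30% | 1.040 | 1.083 | 1.112 |
| 40% | 1.054 | 1.115 | 1.159 |

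The formula does not contain N, so the ratios apply equally to one arm of 90. Patients who leave before T5 supply less information, and the gain is then smaller.

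**3. Bias.** Simulation, N = 180, true slope 0.30, 2,000 runs per setting. The listed model (regression among patients with T6, which is what FIML reduces to here) was compared with maximum likelihood that also includes T5.

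- T6 missing completely at random: listed model 0.298–0.301, no bias.
- T6 missing depending on competence, a predictor in the model: 0.298–0.305, no bias.
- T6 missing depending on T5 change, logistic coefficient 1.5 per SD (odds ratio e^1.5 ≈ 4.5):

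| Missing T6 | ρ = 0.5 | ρ = 0.7 | ρ = 0.8 |
|---|---|---|---|
| 10% | 0.285 | 0.277 | 0.274 |
| 20% | 0.276 | 0.265 | 0.259 |
| 30% | 0.266 | 0.257 | 0.250 |
| 40% | 0.266 | 0.250 | 0.241 |

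The extremes are 0.285/0.30 = 0.95 and 0.241/0.30 = 0.80, so attenuation runs from 5% to 20%. With T5 included, every cell returns to 0.298–0.303. Reversing the direction, so that good responders are lost, gives 0.258 at 30% and ρ = 0.7: the attenuation does not depend on which end is lost.

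Under this response-related loss the difference in standard error is smaller than in step 2: 0.0775 against 0.0776 at 10% missing, and 0.0819 against 0.0796 at 30% (both ρ = 0.7). Bias, not precision, is then the main cost.

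**4. Milder selection, fuller model.** A separate simulation with three further covariates, 10–38% missing T6 and odds ratios of 1.5–3 per SD gave no bias when loss was unrelated to outcome and about 1–11% attenuation when it depended on interim response. The listed model's standard error was about 0–8% larger. Including T2–T5 brought the slope back to about its full-data value.

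**The case against.** **The article does not rule the fix out.** A reader might infer that FIML cannot use the interim scores. The text does not support that. FIML is mentioned as one example of what Mplus offers, auxiliary variables are neither planned nor excluded, and a condensed article may leave such detail to a fuller plan. This stands, and it limits the point to the model as listed. But the article does set out the criterion, the predictors and the missing-data method, so the point proposes a concrete improvement to a stated method; it does not complain of silence.

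**Dilution is not established.** A reader might also infer that the competence effect is diluted. That requires loss at T6 tied to interim response beyond the predictors. The Dropout policy describes leaving treatment, including after early remission, which makes such loss plausible. But leaving treatment is not the same as missing the T6 assessment, and no T6 missing rate is given.

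**The criterion suits the question.** The hypotheses concern pre–post change and response at post-treatment. This stands, and the estimand should stay.

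**The size may be small.** A check with odds ratio 2 per SD and autoregressive residuals of 0.8 gave, at 35% missing, a slope of 95–97% of its full-data value and a standard error 3–6% larger. A bias of about 0.015 against a standard error near 0.095 is minor. Early leavers may also lack competence ratings, since two sessions from different phases are needed, and nesting within therapists was not simulated. Nor does the article give a power figure from which a rate of false null results could be derived. All of this stands as a limit on the size.

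**More parameters in small arms.** Four auxiliary variables add parameters to models with about 90 patients. This is a real but small cost. A growth model would cost more: it imposes a time shape and could link competence to scores obtained before the rated session. Auxiliary variables avoid both.

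**Conclusion.** The point holds for the model as listed. Patients without T6 add essentially nothing to the competence slope although their T2–T5 scores are collected. The standard error is about 0–3% larger near 10% missing and about 4–8% larger near 30% with ρ of 0.5–0.7 (11% at ρ = 0.8). Attenuation is conditional: none if T6 is missing completely at random or depends only on the predictors, about 1–11% under moderate response-related loss, and up to about 20% under the strongest selection tried. The missing rate, the correlations, the slope and the selection strength are all assumptions.

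The documents do not support saying that FIML is unable to use the interim scores, that the effect is in fact diluted, or that the difference score is at fault. This is a cheap improvement to an adjunct project and does not bear on the DBT-PTSD versus CPT comparison.

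**What to change.** In the data-analysis paragraph of Adjunct project I, keep the T1–T6 CAPS-5 change as criterion and estimand, and add a statement such as: *In the models for hypotheses 1, 2a and 2b, CAPS-5 at T2, T3, T4 and T5 enters the FIML likelihood as auxiliary variables (saturated correlates). If a model does not converge, the auxiliary set is limited to T4 and T5.*

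The cost is one or two sentences and a few lines of Mplus code, with no new data and no change to the hypotheses. The only downside is the extra parameters in arms of about 90, which the fallback to T4–T5 limits. Fixing this before the outcome data are analysed also avoids choosing auxiliary variables after seeing results.

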### Adjunct project II: Experimental validation of therapy response

#### Background

Besides psychometric measures, behavioural and neurobiological data can be used to validate treatment effects. Several studies have shown that functional (and in part also structural) alterations in PTSD are amenable to change by psychotherapy [109]. While intrusions are characterized by increased traumatic memory processing, dissociation is related to reduced memory processing up to amnesia [110]. Clinically, intrusions are accompanied by physiological hyperarousal, while dissociation is characterized by reduced arousal and, in extreme cases, a shut-down of sensory and motor processes. Dissociative responses have been shown to be stress-related [111] and reduced startle responses during dissociative states have been demonstrated [112]. The interaction of dissociation and learning processes has been investigated: Pavlovian conditioning was disturbed during dissociation in patients with BPD [57], and dissociation predicted poor outcome of standard DBT and of DBT-PTSD [61, 113]. Recently, a neurobiological model of PTSD has been proposed, differentiating processing of intrusive hyperarousal as opposed to dissociation with emotional overmodulation [114]. Intrusive responses are characterized by increased sympathetic activity (elevated heart rate and blood pressure), whereas dissociative responses are characterized by no change or a decrease in heart rate [115]. On the neural level, several studies have demonstrated amygdala hyperactivity together with medial prefrontal hypoactivity [116–118] to be associated with intrusive hyperarousal. On the other hand, dissociative responses are characterized by an increase in medial prefrontal and insular activity [115, 119, 120]. Amygdala activity was negatively correlated with dissociation levels during an Emotional Working Memory Task (EWMT; [121]). As intrusions and dissociation interfere with attention, the Stroop task has been widely used in PTSD. PTSD patients demonstrated increased interference to trauma-related material in the Emotional Stroop Task (EST; e.g., [122–124]). Imaging studies have demonstrated over-activation in the dorsal anterior cingulate cortex (dACC) as well as the insula in PTSD related to sexual abuse [125, 126]. Psychotherapy response was found to be related to a decrease of this over-activation in sexual abuse-related PTSD [127].

#### Hypotheses

Improvement of PTSD symptoms from pre to the end of the high frequency phase of treatment (∆CAPS T1-T5) is correlated with the reduction of dorsal ACC and anterior insula activity (∆BOLD-signal T1-T5) during trauma-related words in the Emotional Stroop Task (EST).Improvement of PTSD symptoms from pre to the end of the high frequency phase of treatment (∆CAPS T1-T5) is correlated with reduction of amygdala activity and heart rate increase (∆BOLD-signal T1-T5) during negative pictures in the Emotional Working Memory Task (EWMT).Exploratively, we will investigate potential differences regarding neural activation patterns between DBT-PTSD responders and CPT responders. As DBT-PTSD includes skills-assisted exposure, we assume that DBT-PTSD will have a stronger effect on intrusions than will CPT. At the neural level, we would therefore expect a stronger reduction of the neural activation patterns of intrusions in DBT-PTSD responders as compared to CPT responders.

Power analyses for the hypotheses, i.e., that “Improvement of PTSD symptoms is correlated with the reduction of i) dorsal ACC activity, ii) anterior insula activity, iii) amygdala activity, iv) heart rate increase” are all tested at the Bonferroni-adjusted level of α_1_ = 0.0125. A large effect (r = 0.5) is assumed for the hypotheses. The assumption of a large effect is in line with the results on Emotional Stroop interference published by Thomaes et al. [127] who found large correlations ranging from 0.64 and 0.74 between improvements on the CAPS and decreased activation of several regions including the dorsal ACC and the anterior insula. Under these assumptions, the sub-sample recruited at the Mannheim and Frankfurt sites will be sufficient to achieve sufficient statistical power of 1-β = 0.86 for rejecting each of the hypotheses at the adjusted α-level of 0.0125 (two-tailed).

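### Adjunct project II: Holm's step-down test could replace single-step Bonferroni for the four correlations at the same 5% family-wise error (minor, optional gain)

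*Protocol article*

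**What the plan says.** The rule is in the Protocol article, Adjunct project II, section Hypotheses, in the paragraph on power. The family has four members: "i) dorsal ACC activity, ii) anterior insula activity, iii) amygdala activity, iv) heart rate increase". They "are all tested at the Bonferroni-adjusted level of" 0.0125. The planning effect is the same for all four: "A large effect (r = 0.5) is assumed for the hypotheses". On that basis the Mannheim and Frankfurt sub-sample is said to give "sufficient statistical power of 1-β = 0.86" "for rejecting each of the hypotheses at the adjusted" level, two-tailed.

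The article does not give the number of scanned patients and mentions no step-down rule. The comparison of DBT-PTSD responders with CPT responders is labelled exploratory and lies outside the four tests.

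**The concern.** The article fixes a multiplicity rule, so this is not a detail left to an analysis plan that we cannot see. Under that rule each of the four p-values must reach 0.0125 whatever the other three show. Once one hypothesis has been rejected, at most three true nulls can remain, and guarding against four is more than a 5% family-wise guarantee needs. Holm's procedure uses this slack; single-step Bonferroni does not.

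At stake is some power in a mechanistic substudy: a real association with a p-value between 0.0125 and its Holm threshold would go unconfirmed although the same data could confirm it at the same family-wise error. Keeping Bonferroni cannot produce a false claim, and the CAPS-5 comparison of the two treatments does not depend on it.

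**Working it through.** **Inputs from the article.** Four tests; two-sided level 0.0125 each; r = 0.5 for each; stated power 0.86; at least 180 patients randomised at three sites, two of which feed this substudy.

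**Assumptions.** The number analysed, N, is not stated, so a range is shown. The residual correlation among the four measures is not stated either; it was varied from 0 to 0.6.

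**1. Level.** 0.05 / 4 = 0.0125, as stated. The 5% family-wise level is not written out, but 4 × 0.0125 = 0.05 implies it.

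**2. Stated power.** With Fisher's z, power = Φ(atanh(r) × √(N − 3) − z), where z = 2.498 for a two-sided 0.0125 and atanh(0.5) = 0.5493.
- N = 45: 0.5493 × √42 = 0.5493 × 6.481 = 3.560; 3.560 − 2.498 = 1.062; Φ(1.062) = 0.856.
- N = 46: 0.865.
- Simulated exact bivariate-normal power at N = 45: 0.861. A noncentral t calculation gives 0.864 at N = 42.

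The stated 0.86 therefore implies about 42 to 46 analysed patients. If the two sites supplied two thirds of 180 (N = 120, an assumption), the formula gives 0.9997. The figure 0.86 thus seems to reflect a much smaller scanned sample.

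**3. Error control of Holm.** Order the four p-values and compare them with 0.05/4 = 0.0125, 0.05/3 = 0.0167, 0.05/2 = 0.025 and 0.05/1 = 0.05, stopping at the first failure. If m of the four nulls are true, the first true null to be rejected comes at step 4 − m + 1 at the latest, so its threshold is at most 0.05/m. Adding over the m true nulls gives at most 0.05, whatever their dependence. Any p-value at or below 0.0125 passes at every step, so Holm rejects all that Bonferroni rejects.

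Simulated family-wise error (N = 45, independent residuals, real effects at r = 0.5):

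| Real effects | Bonferroni | Holm |
|---|---|---|
| 0 | 0.050 | 0.050 |
| 1 | 0.038 | 0.049 |
| 2 | 0.025 | 0.046 |
| 3 | 0.013 | 0.045 |

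**4. Power per test, all four effects real** (simulation; ranges are over the residual correlation):

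| N | r | Bonferroni | Holm |
|---|---|---|---|
| 45 | 0.5 | 0.86 | 0.92–0.94 |
| 60 | 0.5 | 0.95 | 0.98 |
| 80 | 0.5 | 0.99 | 1.00 |
| 120 | 0.5 | 1.00 | 1.00 |
| 120 | 0.3 (assumed) | about 0.80 | about 0.89 |

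**5. Where nothing is gained.** Power to reject at least one hypothesis is identical under both rules (0.97 to 0.999 at N = 45), because the first Holm threshold is the Bonferroni threshold. With one real effect at N = 45, power for it is 0.863 under both. With two real effects and independent residuals it rises only from 0.86 to 0.88, and with three from 0.86 to about 0.91.

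**The case against.** The strongest reply is that nothing here is wrong. The division of 0.05 by 4 is correct, Bonferroni is valid, and 0.86 per test exceeds the 0.80 used in the section Power analyses. All of that stands, and it keeps this a suggestion. It can also be said that the sentence is a power statement, and that 0.0125 is the natural planning level under Holm too. That is fair for the 0.86, but the wording also says how the hypotheses are tested, and it reads as a single-step rule.

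The size of the gain rests on an unstated N. This also stands: the clear gain is at N = 45, and it is gone at N = 120 with the article's own r.

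Two stronger readings are tempting and are not supported.
- A reader might note that the hypotheses join two measures with an *and*, and conclude that joint confirmation is what counts. The chance of rejecting all four at N = 45 does rise more, from 0.58–0.70 to 0.81–0.86. But the article relists the measures as four separate items and gives power for each. Joint success is not a stated criterion.
- A reader might infer that the Emotional Working Memory Task effects are weaker, since the support cited for a large effect comes from a study of Emotional Stroop interference "who found large correlations ranging from 0.64 and 0.74 between improvements on the CAPS". The article assumes r = 0.5 throughout and gives no smaller value, so any gain computed for weaker effects would rest on the reader's own figure.

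Nor is Holm entirely without cost. Its error rate on true nulls is higher than Bonferroni's, though within 5%, and simultaneous confidence intervals kept at the Bonferroni level may not match every Holm decision.

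**Conclusion.** This is a minor improvement confined to Adjunct project II. The stated plan is valid and its figures are consistent with about 42 to 46 analysed patients. Holm gives the same 5% family-wise guarantee under any dependence and never rejects less. If all four correlations are 0.5 and about 45 patients are analysed, power per test rises by about 0.06 to 0.08. The gain falls to about 0.03 at N = 60 and to nil at N = 120. It needs at least two real effects to appear. It would be too much to say that the substudy is underpowered or its error control faulty; the document supports neither statement.

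**What to change.** Replace the single-step rule in the power paragraph of Adjunct project II with:

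> The four p-values are tested with Holm's step-down procedure at a two-sided family-wise level of 0.05 (ordered thresholds 0.0125, 0.0167, 0.025, 0.05).

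Keep 0.86 as the lower bound of power per test under the stated assumptions. Stating the number of scanned patients on which it rests would let a reader judge the gain.

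The cost is one sentence, fixed before the substudy data are analysed, with no extra patients or measurements. If simultaneous confidence intervals are reported, they can stay at the Bonferroni level (98.75% each, from 1 − 0.0125), with a note that they may not agree with every Holm decision.
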